In order to calculate growth velocity, the natural log-transformed values of the baseline and all postbaseline weight assessments for each patient will be calculated. A linear regression model will then be fitted for each patient with a response variable of log(weight) and a predictor variable of time. Growth velocity for each patient will be estimated as the slope arising from the regression model, and will need to be multiplied by 1000 for conversion into the desired unit of grams per kilogram per day. The weight over time for each treatment group will be illustrated graphically and if the log-transformed data clearly deviate from the linearity assumption, a sensitivity analysis will be performed using untransformed data.

Statistical analysis for the primary efficacy variable will be performed using an analysis of covariance model including factors for treatment, feeding regimen (PBM or infant formula), size for gestational age category (SGA or AGA), with baseline weight included as a covariate. For the comparison between treatment groups, the point estimate and the associated 95% confidence interval and *P* value from the model will be presented.

The assumptions of normality and homogeneity of variance will be assessed by inspection of normal probability plots and residual plots. If either assumption is clearly not met, a corresponding nonparametric analysis will be performed (using the same analysis of covariance model, but using ranked response and covariate) to check the robustness of the results.

- Change from Baseline in body weight (g) at 3 months,
- Body weight (g) at 12 and 24 months corrected age,
- Change from Baseline in total body length (mm) at 4 weeks and 3 months,
- Body length (mm) at 12 months corrected age,
- Body height (cm) at 24 months corrected age,
- Change from Baseline in head circumference (mm) at 4 weeks and 3 months,
- Head circumference (mm) at 12 and 24 months corrected age

will be analyzed using an analysis of covariance approach similar to that used for the primary endpoint. No logarithmic transformation will be performed for these endpoints. Time to readiness for discharge and time to discharge will be analyzed using an analysis of variance model.

Readmission to hospital within 1 month of discharge and growth restriction will be analyzed using a logistic regression model with treatment, feeding regimen (PBM or infant formula), and size for gestational age category (SGA/AGA) as explanatory variables.

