### 3.6 Study Treatments

#### 3.6.1 Method of Assigning Patients to Treatment Groups

Patients will be randomly assigned to receive either rhBSSL or placebo.

An interactive voice recognition system (IVRS) will be used for the randomization. Biostatistics will generate the randomization schedule for IVRS, which will link sequential patient randomization numbers to treatment codes. The randomization will be stratified by feeding regimen (PBM or infant formula) and by size for gestational age category (SGA or AGA). An infant having a birth weight that lies above the 10th percentile for the gestational age on the gender-specific intrauterine growth curves presented by [Olsen et al 2010](#) is defined as AGA. An infant with a birth weight at or below the 10th percentile is defined as SGA. In this study at least 10% of the infants will be SGA at birth and at least 15% of the infants will be fed with PBM.

The randomization numbers will be blocked, and within each block the same number of patients will be allocated to each treatment group. The block size will not be revealed.

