### 3.7.6 Sample Size Calculations

Assuming a true difference in growth velocity between rhBSSL and placebo of 2.25 g/kg/day at 4 weeks and a standard deviation of 7 g/kg/day, 205 evaluable patients in each treatment arm provide 90% power to demonstrate that rhBSSL improves growth velocity compared with placebo (using a 2-sided test with a significance level of 5%). Allowing for 5% of patients to be excluded from the FAS, it is estimated that 432 patients will be randomized. These assumptions are based on the meta-analysis of Sobi's 2 previous Phase 2 studies; the estimate of standard deviation has been increased by 30% to allow for greater variability within the Phase 3 study population.

The sample size calculation was performed using nQuery Advisor software Version 4.0 (Statistical Solutions, Ltd, Cork, Ireland).

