#### 3.8.1 Primary Efficacy Analysis

The null and alternative hypotheses are defined for the primary efficacy variable (growth velocity during the 4 weeks of treatment):

$$H_0: \mu_{\text{rhBSSL}} = \mu_{\text{placebo}}$$

$$H_A: \mu_{\text{rhBSSL}} \neq \mu_{\text{placebo}}$$

In order to calculate growth velocity, the natural log-transformed value of the baseline and all postbaseline weight assessment for each patient will be calculated. A linear regression model will then be fitted for each patient with a response variable of log(weight) and a predictor variable of time. Growth velocity for each patient will be estimated as the slope arising from the regression model, and will need to be multiplied by 1000 for conversion into the desired unit of grams per kilogram per day. The weight over time for each treatment group will be

illustrated graphically and if the log-transformed data clearly deviate from the linearity assumption, a sensitivity analysis will be performed using untransformed data.

Statistical analysis for the primary efficacy variable will be performed using an analysis of covariance model including factors for treatment, feeding regimen (PBM or infant formula), size for gestational age category (SGA or AGA), with baseline weight included as a covariate. For the comparison between treatment groups, the point estimate and the associated 95% confidence interval and *P* value from the model will be presented.

The assumptions of normality and homogeneity of variance will be assessed by inspection of normal probability plots and residual plots. If either assumption is clearly not met, a corresponding nonparametric analysis will be performed (using the same analysis of covariance model, but using ranked response and covariate) to check the robustness of the results.

It is anticipated that the withdrawal rate from the study after randomization will be approximately 15%. For the primary analysis, if patients withdraw before 4 weeks then growth velocity will be derived using weight assessments up to their last available assessment. Sensitivity analyses will be conducted to assess the impact of missing data.

The methods for handling of missing data will be fully described in the SAP.

The primary efficacy variable will be analyzed using both the FAS (the primary population for efficacy evaluation) and PPS (supportive).

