### **3.8.2 Secondary Efficacy Analyses**

The secondary efficacy variables will be analyzed using the FAS only.

The following will be analyzed using an analysis of covariance approach similar to that used for the primary endpoint. No logarithmic transformation will be performed for these endpoints.

- Change from Baseline in body weight (g) at 3 months,
- Body weight (g) at 12 months corrected age,

- Change from Baseline in total body length (mm) at 4 weeks and 3 months,
- Body length (mm) at 12 months corrected age,
- Change from Baseline in head circumference (mm) at 4 weeks and 3 months,
- Head circumference (mm) at 12 months corrected age

The following will be analyzed using descriptive statistics:

- Body weight (g) at 24 months corrected age
- Body height (cm) at 24 months corrected age
- Head circumference (mm) at 24 months corrected age
- Weight-to-length ratio (g/cm) at 4 weeks

The growth restriction is defined as a growth velocity of less than 15 g per kilogram bodyweight per day during the 4-week treatment period and will be analyzed using a logistic regression model with treatment, feeding regimen (PBM or infant formula), and size for gestational age category (SGA/AGA) as explanatory variables. Based on this model, the estimated risk of growth restriction in the rhBSSL and placebo groups respectively, the estimated odds ratio, the associated 95% confidence interval and P-value will be presented. If the risk of growth restriction in the rhBSSL group is statistically significantly lower than in the placebo group, it will be concluded that rhBSSL reduces the risk of growth restriction in preterm infants receiving infant formula or PBM. In addition, the number and proportion of patients in each treatment group with growth restriction will be presented for all patients as well as by feeding regimen and by size for gestational age category.

Time to readiness for discharge will be analyzed using an analysis of variance model. Time to readiness for discharge will be used as the response variable and factors will be included for treatment, feeding regimen (PBM or infant formula) and size for gestational age category (SGA or AGA). For the comparison between treatment groups, the point estimate, the associated 95% confidence interval and P-value from the model will be presented.

Time to discharge will be analyzed using an analysis of variance model similar to that used for time to readiness for discharge.

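### The growth-restriction logistic model omits baseline weight, which the primary ANCOVA of the same growth-velocity variable includes; the planned analysis is valid but may give up some power

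*Protocol*

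**What the plan says.** Growth restriction is the primary variable, growth velocity, cut at 15 g/kg/day. Section 3.8.2 of the protocol fixes its model as a "logistic regression model with treatment, feeding regimen (PBM or infant formula), and size for gestational age category (SGA/AGA) as explanatory variables". The synopsis agrees: "Readmission to hospital within 1 month of discharge and growth restriction will be analyzed using a logistic regression model", with the same three terms.

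For uncut growth velocity, the ANCOVA in Section 3.8.1 has factors for treatment and feeding regimen and "size for gestational age category (SGA or AGA), with baseline weight included as a covariate".

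Three other provisions bear on the point:

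- Section 3.7.7 admits an infant to the full analysis set (FAS) only if a baseline weight and at least one later weight exist. Section 3.8.2 uses the FAS for all secondary efficacy variables.
- Section 3.8.2 attaches a decision rule to the growth-restriction test: a significantly lower risk on rhBSSL leads to a stated conclusion of benefit. No other secondary endpoint has such a rule. Time to readiness for discharge and time to discharge have P values but no rule.
- The other modelled growth outcomes in Section 3.8.2 (weight, length and head circumference up to 12 months) follow an ANCOVA like the primary one.

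**The concern.** Two analyses of one underlying variable use different adjustment sets, and the protocol does not say why. It treats baseline weight as worth adjusting for when growth velocity is continuous and leaves it out when growth velocity is cut.

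The size-for-gestational-age factor is not a full substitute. Section 3.6.1 defines it from the birth-weight percentile within gestational age, so it does not carry absolute weight on Day 1. Including baseline weight would lose no infants, because FAS membership already requires it. Logistic models in this protocol are not confined to the stratification factors either: the neurodevelopment disability model adds further covariates.

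Two things are at stake. First, a test that carries its own conclusion rule may have less power than the collected data allow. Second, if the arms differ by chance in baseline weight, the primary analysis adjusts for it and this one does not, so discordant results would be harder to interpret.

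**Working it through.** **Inputs stated in the protocol.** Section 3.7.6: "Assuming a true difference in growth velocity between rhBSSL and placebo of 2.25 g/kg/day at 4 weeks and a standard deviation of 7 g/kg/day". From these the same section derives its 90% power, at 205 infants per arm and a two-sided 5% level. Allocation is 1:1 (Section 3.6.1: "within each block the same number of patients will be allocated to each treatment group"). The cut-off is 15 g/kg/day (Section 3.8.2). Stratum shares are set at the stated minima, 15% PBM and 10% SGA (Section 3.2).

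**Inputs inferred or assumed.** The placebo mean is not stated. Section 1.5 equates a 2.93 g/kg/day gain with a 20% improvement, so 2.93 / 0.20 = 14.65 g/kg/day. The share of growth-velocity variance that baseline weight explains beyond the two strata (partial R²) is not given, so it is varied.

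**1. The protocol's sample size reproduces.** n per arm = 2 × (1.960 + 1.282)² × 7² / 2.25² ≈ 203.4, rounded up to 204. The t-based calculation gives 205 (power 0.901 at 205, 0.899 at 204). Then 410 / 0.95 = 431.6, rounded up to 432 randomized. The protocol states no power for growth restriction.

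**2. Implied risks and power for growth restriction.**

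- Placebo: Φ((15 − 14.65) / 7) = Φ(0.05) = 52.0%.
- rhBSSL: Φ((15 − 16.90) / 7) = Φ(−0.271) = 39.3%.
- Odds ratio: (0.393 / 0.607) / (0.520 / 0.480) = 0.60.
- Two-proportion power at 205 per arm: 73.4%. Placebo means of 13 to 16 give 72% to 74%.

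**3. Effect of adding baseline weight.** Simulated trials of 410 infants, 4,000 per row, SD 7, two-sided 5% Wald test. Growth velocity = 14.65 + 2.25 × treatment + 7 × (√R² × w + √(1 − R²) × e), with w the standardised baseline weight and e independent noise. The outcome is growth velocity below 15. Simulation error is about 0.7 points per power figure.

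| Partial R² (correlation) | Power without | Power with | Gain, points |
|---|---|---|---|
| 0 | 73.7% | 73.8% | 0.1 |
| 0.02 | 73.2% | 73.3% | 0.1 |
| 0.04 (0.2) | 74.0% | 74.7% | 0.7 |
| 0.05 | 73.5% | 74.9% | 1.4 |
| 0.09 (0.3) | 73.9% | 76.2% | 2.3 |
| 0.10 | 73.8% | 75.7% | 1.9 |
| 0.16 (0.4) | 72.3% | 76.9% | 4.6 |
| 0.20 | 72.9% | 79.4% | 6.5 |
| 0.25 (0.5) | 72.9% | 80.4% | 7.5 |
| 0.30 | 74.0% | 83.3% | 9.3 |

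With no treatment effect (R² of 0, 0.10 and 0.30), type I error was 4.5% to 5.4% with either model.

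**4. Sensitivity to the SD.** Section 3.7.6 says the SD was raised by 30%, so the value before inflation is 7 / 1.3 ≈ 5.4. At SD 5.4, power without and with the covariate is 92.2% and 92.7% (correlation 0.2), 91.7% and 92.7% (0.3), 91.0% and 94.1% (0.4), and 91.5% and 95.5% (0.5). The gain is at most 4 points.

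**5. Effect on the odds ratio.** At SD 7, adding baseline weight moves the average estimate from 0.59 to 0.57 at R² 0.10 and from 0.59 to 0.52 at R² 0.30, as expected when an odds ratio becomes more conditional.

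**The case against.** The strongest defence is that nothing here is wrong. The model contains treatment and both stratification factors and holds its type I error. The same three terms serve for readmission and for the two discharge-time endpoints. No passage promises that growth restriction will reuse the primary model's terms, and Section 3.8 leaves analysis details to the SAP. All of this stands. It is weakened only in that the protocol does name the covariates here, and that readmission and discharge times are not derived from growth velocity.

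The defence is also right that the gain is uncertain. In the simulation, baseline weight is independent of the strata, so a correlation of 0.5 means 25% of variance explained beyond them. Nothing in the protocol supports that value over a smaller one. SGA status may already carry some of the weight information, and the outcome is already expressed per kilogram.

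A reader might infer three stronger things that the documents do not support:

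- That a definite amount of power is lost. The loss is negligible if baseline weight adds little beyond the strata.
- That the omission explains the fall from about 90% power on growth velocity to about 73% on growth restriction. That fall comes from dichotomising; it is present at R² = 0.
- That the simpler model has no merit. Its odds ratio is less conditional, and its group risks need no averaging over weight.

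The imbalance argument is also limited. Over repeated randomisations, the planned test's error rate already allows for chance imbalance. The point concerns precision and the interpretation of one realised trial.

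**Conclusion.** The inconsistency is real and unexplained, but it is a matter of efficiency and consistency, not an error in the planned analysis. In the settings examined, adding baseline weight left power essentially unchanged or raised it, without raising type I error beyond simulation noise. At SD 7, a placebo mean near 14.65 and 205 infants per arm, the gain is about 0 to 2 points for partial R² up to 0.10, 4 to 5 at 0.16, and about 7 at 0.20 to 0.25. It is smaller, on power already above 90%, if the SD is nearer 5.4. These figures rest on an inferred placebo mean, normally distributed growth velocity, strata with no effect of their own, and a partial association that the protocol does not give. The case for acting is the low cost and the conclusion rule attached to this endpoint, not a demonstrated loss.

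**What to change.** Before the scheduled unblinding, add baseline weight to the growth-restriction logistic model in Section 3.8.2 and the synopsis, so that it has the same terms as the primary ANCOVA. Obtain each arm's estimated risk by averaging model predictions over the whole FAS with treatment set to that arm. Show these standardised risks beside the odds ratio, and state that the odds ratio is conditional on baseline weight. If the sponsor prefers the three-term model, give the reason in the text.

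The cost is one covariate in the protocol and SAP wording. It needs no new data and excludes no infant. The one side effect is the more conditional odds ratio, which the standardised risks address.

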#### **3.7.1 Primary Efficacy Endpoints**

The primary efficacy variable is growth velocity in grams per kilogram per day during 4 weeks of treatment.

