#### **3.7.2 Secondary Efficacy Endpoints**

In addition to the primary efficacy endpoint, the following secondary efficacy endpoints will be evaluated to support the primary objective:

- Change from Baseline in body weight (g) at 3 months
- Body weight (g) at 12 months corrected age
- Change from Baseline in total body length (mm) at 4 weeks and 3 months
- Body length (mm) at 12 months corrected age

The following secondary efficacy endpoint will be evaluated to support the objective “To determine the effect of rhBSSL treatment in decreasing risk of growth restriction”:

- Growth restriction, defined as growth velocity <15 g per kilogram bodyweight per day during 4 weeks of treatment

The following secondary efficacy endpoints will be evaluated to support the objective “To determine the effect of rhBSSL treatment in shortening the time of hospital stay”:

- Time to readiness for discharge. This endpoint will be defined as the time from Baseline when all of the following criteria have been fulfilled: a sustained weight gain, ability to maintain normal body temperature, ability to suckle feed, and ability to maintain stable cardiorespiratory function.
- Time to discharge

The following secondary efficacy endpoints will be evaluated to support the objective “To determine the effect of rhBSSL treatment in improving early development”:

- Change from Baseline in head circumference (mm) at 4 weeks and 3 months
- Head circumference (mm) at 12 months corrected age
- Time from Baseline to 150 mL/kg/day of enteral feeding

The following secondary efficacy endpoint will be evaluated to support the objective “To determine the effect of rhBSSL treatment on decreasing readmittance to hospital”:

- Readmission to hospital within 1 month of discharge

The following secondary efficacy endpoints will be evaluated to support the objective “To determine the effect of rhBSSL treatment on increasing the levels of DHA and AA”:

- Levels of DHA and AA at 4 weeks

The following secondary efficacy endpoints will be evaluated to support the objective “To determine the effect of rhBSSL treatment on neurodevelopment”:

- Bayley-III scores at 24 months corrected age
  - Cognitive domain composite score
  - Language domain composite score
  - Motor domain composite score
  - Social-emotional domain composite score
  - Adaptive domain composite score

- Scaled scores for each subtest and for the cognitive and social-emotional domains (in total 16 scaled scores)

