### 3.8 Statistical Analysis

Demographic data and background characteristics will be summarized using descriptive statistics. Continuous variables will be summarized using the mean, the standard error of the mean, the median, the minimum value, and the maximum value. Categorical variables will be summarized using frequency counts and percentages. All data will be listed in data listings.

Details of all analyses will be described in the statistical analysis plan.

Statistical analysis will be performed using SAS software Version 9.1 or later (SAS Institute, Inc, Cary, North Carolina, United States). All statistical tests will be 2-sided and performed using a 5% significance level, leading to 95% (2-sided) confidence intervals.

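### The growth-restriction conclusion in Section 3.8.2 rests on its own unadjusted 5% test and does not require a favourable primary result, although it is the primary variable dichotomised

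*Protocol*

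**What the plan says.** Section 3.7.1 sets one primary variable: "The primary efficacy variable is growth velocity in grams per kilogram per day during 4 weeks of treatment". Section 3.8.1 gives its null and alternative hypotheses and states the model: "analysis of covariance model including factors for treatment, feeding regimen (PBM or infant formula), size for gestational age category (SGA or AGA), with baseline weight" as covariate.

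Section 3.7.2 lists as a secondary endpoint "Growth restriction, defined as growth velocity <15 g per kilogram bodyweight per day during 4 weeks of treatment", under its own secondary objective of decreasing the risk of growth restriction. Section 3.8.2 analyses it by logistic regression on treatment, feeding regimen and size for gestational age, and states that "the estimated odds ratio, the associated 95% confidence interval and P-value will be presented". It then adds a decision rule: if the risk under rhBSSL is "statistically significantly lower than in the placebo group, it will be concluded that rhBSSL reduces the risk of growth restriction".

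Section 3.8 sets the level: "All statistical tests will be 2-sided and performed using a 5% significance level, leading to 95% (2-sided) confidence intervals". Sections 3.7.7 and 3.8.2 place the secondary efficacy variables in the full analysis set, which is also the primary set for the primary variable. The protocol contains no testing order, no adjustment across endpoints, and no sentence that makes the growth-restriction conclusion depend on the primary result.

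**The concern.** Growth restriction is the only secondary endpoint with a written conclusion rule. For readmission, the 24-month Bayley-III scores and the disability composite, Section 3.8.2 promises estimates and confidence intervals. For time to readiness for discharge it promises a P value but no conclusion. Pre-declaring an efficacy conclusion for one secondary endpoint makes its position relative to the primary matter.

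That position matters more here because the endpoint is not a separate outcome. It is the primary variable with a threshold applied, in the same patients over the same weeks. Followed as written, the rule lets the report conclude that rhBSSL reduces growth restriction while the primary analysis shows no significant difference in growth velocity. The report would then give two answers on growth from one measurement, and the chance of a false favourable statement about growth would be larger than the primary test alone implies.

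**Working it through.** **Inputs.** From Section 3.7.6: difference 2.25 g/kg/day, SD 7 g/kg/day, 205 evaluable per arm, 90% power, 2-sided 5%, 432 randomised. From Section 3.7.2: cut-off 15 g/kg/day. The protocol gives no placebo mean. Section 1.5 reports a Phase 2 gain of 2.93 g/kg/day, described as a 20% improvement, which implies 2.93 / 0.20 = 14.65 g/kg/day. This is an assumption, so the placebo mean is varied from 12 to 20.

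**1. The plan's own figure.** Normal approximation: n per arm = 2 × (1.960 + 1.282)² × 7² / 2.25² ≈ 203.4, rounded up to 204. The noncentral t distribution gives 205 as the smallest n with at least 90% power (90.1%). Then 410 / 0.95 = 431.6, rounded up to 432. The stated sample size is reproduced.

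**2. Correlation of the two tests under no effect.** Let Z1 be the test on the mean and Z2 the test on the proportion below 15, both signed so that positive favours rhBSSL. With c = (15 − mean) / 7 and p = Φ(c), their correlation is ρ = φ(c) / √(p(1 − p)). At a mean of 14.65: c = 0.35 / 7 = 0.05, p = 0.520, and ρ = 0.398 / 0.4996 ≈ 0.80.

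**3. Error rates from the bivariate normal.**
- Either test significant, any direction: 1 − P(|Z1| < 1.96, |Z2| < 1.96).
- False favourable claim by either route: 1 − P(Z1 < 1.96, Z2 < 1.96).
- Favourable growth restriction without a favourable significant primary: the previous line minus 2.5%. At 14.65 this is 3.91% − 2.50% = 1.41%.

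| Placebo mean | p | ρ | Either test, any direction | Favourable, either route | Growth restriction only |
|---|---|---|---|---|---|
| 12 | 0.666 | 0.772 | 7.98% | 3.99% | 1.49% |
| 14.65 | 0.520 | 0.798 | 7.82% | 3.91% | 1.41% |
| 16 | 0.443 | 0.795 | 7.84% | 3.92% | 1.42% |
| 18 | 0.334 | 0.772 | 7.98% | 3.99% | 1.49% |
| 20 | 0.238 | 0.726 | 8.22% | 4.11% | 1.61% |

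Two independent tests would give 1 − 0.95² = 9.75% in the fourth column. The strong correlation is why the actual figure is nearer 8%.

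**4. Check with the planned models.** The ANCOVA and logistic models were simulated with 410 patients and 20,000 null trials per scenario, at placebo means of 14.65 and 18. Assumptions were 15% fed pasteurised breast milk, 10% small for gestational age, and a correlation of 0 or 0.3 between baseline weight and growth velocity. Each test alone rejected in 4.8% to 5.2% of trials. Either test was significant in 7.9% to 8.3%, a favourable claim by either route occurred in 4.0% to 4.2%, and growth restriction was favourable with a non-significant primary in 1.5% to 1.6%.

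**5. With a real effect** (8,000 trials, placebo mean 14.65). At 2.25 g/kg/day, power is 90% for the primary and 73% for growth restriction, and growth restriction alone is favourable and significant in 1.3% of trials. At an effect of 1.1 g/kg/day, about half the design effect, that last figure is 4.6%.

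**The case against.** The strongest reply is that no stated error rate is broken. Section 3.8 sets 5% per test and promises no control across primary and secondary endpoints. There is one primary variable with one pair of hypotheses, growth restriction is labelled secondary, and it answers its own objective. All of this stands: the primary test's 5% is untouched, and nothing in the plan lets the secondary conclusion replace the primary one.

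A second reply is that Sections 3.7 and 3.8 refer details to a statistical analysis plan, which is not at hand and may set a testing order. It may. But the protocol does more than stay silent: it writes down when the conclusion will be drawn. A condition added in the analysis plan would change that rule, so the protocol wording needs correcting or expressly superseding.

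Three stronger readings are tempting and are not supported:

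- A reader might infer from the 8% figure that the chance of a false efficacy claim exceeds 5%. It does not. That figure includes results against rhBSSL, and the rule applies only when the risk is lower under rhBSSL. The comparable figures are about 4% against 2.5%.
- A reader might infer that leaving baseline weight out of the logistic model is an error. Both randomisation strata are in the model, and omitting a prognostic covariate does not inflate the type I error of a randomised comparison. In the simulation the growth-restriction test alone stayed at 4.9% to 5.1%.
- A reader might infer that every secondary P value needs ordering or relabelling. No other secondary endpoint carries a conclusion rule, so the defect does not reach them.

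**Conclusion.** The point holds as a moderate defect in wording that the protocol itself fixes. A formal favourable conclusion on a dichotomised form of the primary variable depends only on its own unadjusted 2-sided 5% test. With no true effect, the chance of a false favourable growth claim by either route is about 4% instead of 2.5%. The part due to the missing condition, a false growth-restriction conclusion without a favourable significant primary, is about 1.5%.

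These sizes assume roughly normal growth velocities, SD 7, 205 per arm and a placebo mean between 12 and 20 g/kg/day. They vary by only about 0.2 percentage points over that range. The primary inference and the sample size are not affected.

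**What to change.** Add to Section 3.8.2, directly after the conclusion rule: the conclusion on growth restriction is drawn only if the primary analysis is significant at the 2-sided 5% level in favour of rhBSSL; otherwise the growth-restriction P value is descriptive. Carry the same sentence into the statistical analysis plan before unblinding.

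With this condition a favourable growth-restriction claim can occur only after a favourable primary, so the false favourable rate over the two tests returns to 2.5%, and the 2-sided rate for the ordered pair is at most 5%. Sample size and primary power do not change. The cost is that no growth-restriction claim is available when the primary fails. This forgoes the claim in about 1.3% of trials under the design effect, and in about 4.6% if the true effect is 1.1 g/kg/day.

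Optionally, add baseline weight to the logistic model, for precision and consistency with the primary model. It is already collected, and its absence is not an error.
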